### Recruitment and trial procedures

Healthy volunteers will be recruited through approved postings in the community. The CAMH Research Registry will also be used to recruit participants for this clinical trial. Upon REB approval to use the Research Registry as a recruitment strategy, authorized research personnel will search and contact potential research participants included within the member database of the Research Registry for study participation. This clinical trial will also be posted on the Research Registry website, as well as the public CAMH website. Once posted, interested participants can use the “Find a CAMH study” feature to explore clinical trials that they are interested in.

Interested individuals will be pre-screened by study staff with the REB approved “pre-screen form” to determine preliminary eligibility. If deemed eligible based on this form, participants will be invited to complete informed consent and the begin the official screening procedures of the study. Study staff will obtain written, signed informed consent from each participant. The study team will maintain records for the number of people approached, screened, eligible, withdrawn, and the reasons for non-enrollment. Any research information recorded for, or resulting from, participation in this research study prior to the date that the participant formally withdrew their consent will be retained and may continue to be used and disclosed by the investigators for research purposes; however, no new data will be collected.

### Randomization, blinding, and allocation concealment methods

Study staff will confirm eligibility and assign each participant a unique trial number. As all participants will receive oral PL at visit 1 and oral OLA at visit 2 of each cycle phase, no randomization of investigational products will occur. Study staff will remain unblinded to ensure accurate scheduling of visits during each phase. Both INP and INI will be administered at every MRI visit: INP will always be delivered before the first scan and INI before the second scan. Participants will be blinded to the order of these interventions and will not know whether they have received OLA or PL. Oral OLA and PL will be dispensed by the pharmacy in identical capsules packaged in blister packs. INI and INP will be transferred from their respective vials into identical, unlabeled metered spray bottles to maintain participant blinding.

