### Study design

Fig 2 provides a comprehensive overview of the entire study design and protocol. In a single-blind crossover study, every participant is given four different treatment conditions (INP/PL, INI/PL, INP/OLA, or INI/OLA) on two separate occasions. This means that each treatment is administered once during each menstrual cycle phase, resulting in participants receiving all conditions twice over the course of the study. All participants will receive oral PL at visit 1 and oral OLA at visit 2 of each cycle phase. Study visits will take place 2–6 weeks apart to ensure specific menstrual phase across the four visits and adequate washout between conditions. Participants will undergo two visits during the follicular phase of the menstrual cycle. To ensure a regular menstrual cycle, participants will be asked to provide information about the length of their last three cycles. Average cycle duration will be calculated to determine cycle phases. One cycle duration is defined as from cycle onset date (Day 1) to the day before the next cycle onset (i.e., Day 1 is defined as the first day of menstruation). Based on this, participants will be invited to complete the visits during the specific windows of their follicular and luteal phase. Menstrual cycle phases will be identified using calendar-based counting. The onset of their menstruation will be considered as the first day of the current menstrual cycle and will be denoted the start of the follicular phase. The follicular phase visit can take place starting 2 days after the start of the current menstrual cycle and no more than 17 days apart from the start of the subsequent cycle (i.e., they will be scanned between days 3 and 11 of their cycle). The luteal phase will be defined in the time frame of a maximum of 10 days but no less than 3 days before the start of the subsequent cycle (i.e., between day 18–25). Measurement of serum sex hormones (progesterone, estrogen, luteinizing hormone (LH) and follicular stimulating hormone (FSH)) will be done at each visit to confirm cycle phase.

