**Fig 2 pone.0352262.g002:**
[figure not shown]
Summary of overall study design and visit protocol. Following screening, eligible participants will be enrolled to take part in the 2x2 crossover study. Each participant will undergo a total of four primary study visits, two per cycle phase (follicular and luteal). Participants will receive oral placebo (PL) on days 0 and 1 of the first visit of each phase, and oral olanzapine (OLA) on days 0 and 1 of the second visit of each phase. At each visit, intranasal placebo (INP) will be administered prior to scan #1, and intranasal insulin (INI) prior to scan #2. Figure created on BioRender.com.

Each of the study periods will involve a three-day protocol (Fig 2): administration of OLA 5 mg (or PL) HS on day 0, OLA 10 mg (or PL) HS on day 1, and cognitive testing and MRI scanning on day 2. There will be two MRI scans on day 2, the first following administration of INP and the second following 160 IU of INI. Administration of INP always precedes INI as the effect of insulin in the brain is known to last for 2 hours, and counterbalancing the administration of INI first will require a much longer washout period/study visit, adding participant burden.

The two acute OLA doses of 5 mg and 10 mg are chosen for reasons of practicality and safety in line with previous studies [24,39]. The INI dose is the maximum safest dose that has been administered in humans and is chosen based on earlier work in nine healthy males showing a dose-dependent relationship on regional brain activity, with the strongest effects being observed after 160 IU [27]. This dose has been shown to induce changes in the brain in females as well [40,41]. Blood samples will be drawn before and after the MRI to measure insulin spillover. Dose-dependent spillover of INI into peripheral circulation has been reported, although the observed brain responses were not correlated with this transient rise in circulating insulin [27]. OLA levels will be measured to assess adherence.

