### Statistical analysis

The primary outcome is rsFC. Given the exploratory nature of this study, a formal power calculation was not performed. The sample size (N = 15) was instead informed by prior neuroimaging studies examining the effects of INI on MRI-derived outcomes, which have which have typically included 9–25 participants and reported large effect sizes (Cohen’s d: 0.8 to 1.4, f: 0.4–0.6). In the context of a within-subject crossover design, which reduces between-subject variability and increases statistical efficiency, this sample size is expected to provide adequate sensitivity to detect moderate-to-large effects in resting-state functional connectivity.

To address hypothesis #1, which is the difference in brain insulin sensitivity between cycle phases, analyses will be restricted to visits in which participants receive the oral PL. A linear mixed effects model will be conducted with rsFC as the dependent variable and fixed effects for intranasal condition (i.e., INI vs. INP), menstrual phase (follicular vs. luteal), and their interaction. Participant will be included as a random intercept, with age and BMI entered as covariates. The primary effect of interest is the intranasal condition x menstrual phase interaction, which tests whether the effect of INI (relative to INP) differs between follicular and luteal phases. Planned simple effects will assess (i) the effect of INI vs. INP within each phase, and (ii) the difference in INI-induced change (INI – INP) between phases.

To test the effect of OLA within each phase, a second linear mixed effects model will be conducted including all visits. Fixed effects will include intranasal condition (INI vs. INP), oral condition (OLA vs. PL), menstrual phase (follicular vs. luteal) and all interaction terms. Participants will be modeled as a random intercept, with age and BMI as covariates. The primary term of interest is the intranasal condition x oral condition x menstrual phase interaction, which tests whether OLA modifies INI-induced effects differently across cycle phases.

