### Limitations and measures to minimize bias

It is recognized that the single-blind nature of this study is a limitation but required to ensure the proper distribution of study conditions across cycle phases. The trial is registered with a publicly available, free-to-access, searchable clinical trial registry before approaching the first participant to avoid bias selection of the reported result(s). Furthermore, study staff administering and scoring the extra-scanner cognitive assessments will be blinded to the INI/INP allocation to minimize any bias (they will not be involved in transferring the product into the nasal spray bottle).

Participants may experience mild subjective effects related to the study interventions (e.g., nasal irritation with intranasal administration or transient sedation with OLA), which could potentially compromise the single-blind design. To mitigate this, placebo conditions will be matched as closely as possible in appearance and administration, and participants will remain unaware of treatment allocation. Furthermore, a questionnaire will be completed at each visit to assess participant blinding success. Participants will be asked whether they believe they received the OLA or PL at that visit, as well as whether they received INP or INI they received prior to each MRI scan, and to rate their confidence in these judgements. The James’ Blinding Index (BI) will be calculated from these responses [52].

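### With oral placebo always first and olanzapine always second within each phase, the OLA x INI contrast is identical to visit order x scan order, so hypothesis 2 rests on an untestable assumption that the plan does not state

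*Protocol article*

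**What the plan says.** The Protocol article fixes both orders for everyone.

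- **Oral order.** Study design: "All participants will receive oral PL at visit 1 and oral OLA at visit 2 of each cycle phase". The Fig 2 legend agrees, placing "oral olanzapine (OLA) on days 0 and 1 of the second visit of each phase". The section on randomization, blinding and allocation concealment draws the consequence that nothing is randomised: "oral PL at visit 1 and oral OLA at visit 2 of each cycle phase, no randomization of investigational products will occur".
- **Intranasal order.** The same section: "INP will always be delivered before the first scan and INI before the second scan". Study design gives a reason for this: the duration of the insulin effect and the burden of a longer visit. The article gives no corresponding reason for the oral order.
- **Design label.** The Fig 2 legend says that "eligible participants will be enrolled to take part in the 2x2 crossover study".
- **Model.** The olanzapine model in Statistical analysis contains intranasal condition, oral condition, phase and all their interactions, with a random intercept, age and BMI. It has no visit or order term. The three-way interaction is its primary term, described as one "which tests whether OLA modifies INI-induced effects differently across cycle phases".
- **Hypothesis 2.** Objectives and hypotheses words it within a phase: olanzapine is to block the INI effects during the follicular phase.
- **Limitations.** The section says that the "single-blind nature of this study is a limitation but required to ensure the proper distribution of study conditions across cycle phases", and it discusses possible unblinding. It does not mention order.

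**The concern.** A crossover protects a treatment contrast from time and order effects because participants differ in the order in which they receive the treatments. Here there is one oral order, so that protection is absent. The fixed scan order adds to the problem: a habituation or fatigue effect that changes the scan-1 to scan-2 difference on a repeat visit falls exactly on the OLA x INI contrast.

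The predicted finding for hypothesis 2 is an INI-INP change at the follicular placebo visit that is reduced at the follicular olanzapine visit. A scan-to-scan change that fades once the participant knows the scanner produces the same pattern with no drug effect. An analyst following the plan as written would report the result as olanzapine modifying insulin action, and the limitations section would give the reader no warning.

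**Working it through.** **1. Identity of the contrasts.** Let Y(v,s) be connectivity in the follicular phase at visit v (1 or 2 within the phase) and scan s (1 or 2). Under the stated order, PL is v = 1, OLA is v = 2, INP is s = 1 and INI is s = 2.

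OLA x INI = [Y(OLA,INI) - Y(OLA,INP)] - [Y(PL,INI) - Y(PL,INP)]
= [Y(2,2) - Y(2,1)] - [Y(1,2) - Y(1,1)]
= visit order x scan order.

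**2. Check on the design matrix.** The planned olanzapine model has 8 fixed-effect columns (intercept, three main effects and all interactions; age and BMI do not bear on this). Adding within-phase visit order and its interactions with scan and phase makes 12 columns.

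| Oral order | Correlation of oral condition with within-phase visit order | Rank with order terms |
|---|---|---|
| Fixed PL then OLA (15 participants) | 1.00 | 8 of 12 |
| Half PL-first, half OLA-first (16, for balance) | 0.00 | 12 of 12 |

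The fixed-order result was the same for every arrangement of phases tried: both follicular visits first, phases alternating, and mixed starting phases. Each olanzapine term equals its visit-order counterpart.

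**3. Which order effects matter.** Let a be an additive shift at the second visit and g a shift in the scan-2 minus scan-1 difference at the second visit.

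- Additive shift: (Y + a) - (Y + a) removes a from each INI-INP change, so it cancels. In simulation with a = 0.8 SD and no drug effect, rejection was 5.3% for the follicular contrast and 5.1% for the three-way term.
- Shift in the scan difference: the follicular OLA x INI estimate is biased by all of g. The three-way term is biased by g(follicular) - g(luteal), which is zero when the two are equal.

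**4. Size, under assumed g.** The documents give no figure for g. N = 15 and α = 0.05 come from Statistical analysis. Two-sided testing and independent changes across visits are assumptions. The test is a one-sample t on per-participant contrasts with 14 df and critical value 2.145, which simplifies the mixed model.

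- *g in units of the SD of the INI-INP change.* The contrast is a difference of two changes, so its SD is √2. For g = 0.5, d = 0.5/√2 = 0.354, noncentrality = 0.354 x √15 = 1.37, rejection 24.8%. For g = 0.3, noncentrality is 0.82 and rejection 12.0%.
- *g in units of the residual SD of a single scan.* The contrast combines four scans, so its SD is 2. For g = 0.5, d = 0.25, noncentrality 0.97, rejection 14.7%. For g = 1.0 it is 44% and for g = 1.5 it is 77%.
- *Three-way term.* With g equal in both phases, simulated rejection stays near 5%. With g = 0.5 in the follicular phase only, it is 14.7% in change-SD units (SD of the contrast 2) or 9.8% in residual-SD units (SD √8).

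**5. After counterbalancing.** In simulation with 15 participants split between the two oral orders, rejection without a drug effect was 4.5% to 5.5% for both contrasts in every scenario tried.

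**The case against.** The strongest reply is that the named primary term is better protected than the fixed order suggests. Additive effects of visit, season or scanner drift cancel, and the three-way term cancels any visit-order x scan-order effect that is equal in both phases. It also cancels gradual linear habituation. If the scan-to-scan change falls as 3, 2, 1, 0 over the four visits, the three-way contrast is (2 - 3) - (0 - 1) = 0 when both follicular visits come first, and (1 - 3) - (0 - 2) = 0 when phases alternate. This stands. It does not help hypothesis 2 as worded, which is a within-follicular contrast without that cancellation.

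It is also fair that the study is called exploratory, that no document figure supports any particular g, and that the condensed article may omit a reason for the oral order that the full protocol gives. A reason would explain the order without removing the aliasing. The 2–6 week spacing deals with carry-over and leaves order effects untouched.

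Two stronger readings are tempting and are not supported. A reader might infer that no olanzapine effect can ever be attributed to the drug. The documents support only that attribution needs the assumption of no visit-order x scan-order effect. A reader might also infer that phase is confounded with visit number, so that habituation would mimic hypothesis 1 too. That would need everyone to start in the same phase. The article does not state the phase order, and it refers to an assigned phase in Study visits 1–4, so this remains conditional.

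**Conclusion.** The point holds in this form. The aliasing is exact, follows from the allocation stated in the article, and cannot be repaired by any covariate or model. Statistical analysis nevertheless attributes its interaction to olanzapine, and the limitations section is silent, so the plan as written could lead to an unsupported causal statement.

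Hypothesis 2 is fully exposed. The three-way term is exposed only to an order effect that differs by phase. An assumed order effect of 0.5 SD gives a false follicular finding about 25% of the time (SD of the INI-INP change) or about 15% (residual SD). These percentages rest on the assumed size, independent changes across visits and a paired-contrast test. The identity of the contrasts rests on none of them.

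**What to change.** **1. Restrict the claim (Statistical analysis; Limitations and measures to minimize bias).** State that oral condition is aliased with within-phase visit order, and OLA x INI with visit order x scan order. Report the fixed-order contrast as *OLA/second visit*. Make attribution to olanzapine conditional on no visit-order x scan-order effect, and do not claim olanzapine inhibition from this contrast alone. This costs a few sentences and weakens the conclusion to what the design supports.

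**2. Where an amendment is feasible, vary the order.** Let the pharmacy randomise PL/OLA order within phase for participants or phase blocks not yet started. It already supplies matched products ("Oral OLA and PL will be dispensed by the pharmacy in identical capsules packaged in blister packs"), and staff can still schedule visits from menstrual dates. Then add visit order and intranasal x visit order as a sensitivity analysis.

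The second step has real costs. It needs ethics and regulatory amendments and a pharmacy list. It reaches few participants: Recruitment status and study timeline reports 13 enrolled of a planned 15, with six completed and three withdrawn, which leaves 13 - 6 - 3 = 4 active. Reversed order would occur only late in enrolment and so be tied to calendar time. The order term also inflates the standard error of the olanzapine contrast. With k of 15 reversed, the ratio is √{[1/(15-k) + 1/k]/4 ÷ (1/15)}, which is 1.47 for k = 2 and 1.25 for k = 3, an increase of 47% or 25%. For most of the sample, step 1 is therefore the workable remedy.

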### Study assessments

#### Screening visit.

Prior to inviting participants to complete the consent form and begin the screening visits of the study, participants will be asked a series of eligibility-related questions through a telephone pre-screen to act as an initial check of eligibility and safety.If the participant has been deemed eligible, they will proceed to the screening visits of the study for informed consent and thorough assessment of eligibility. Screening will begin with obtaining informed consent, followed by a review of each participant’s medical history and demographic information. Participants will undergo fasting bloodwork, including fasting glucose, insulin, c-peptide, lipid profile, HbA1c, complete blood count, prolactin, vitamin B12, electrolytes, thyroid function, and liver and kidney function tests. Anthropometric measures will also be collected, including height, weight, blood pressure, and waist circumference. Edinburgh Handedness Inventory (EHI) will be used to assess hand dominance or laterality [44]. Psychiatric screening will be conducted using the Mini-International Neuropsychiatric Interview (MINI) [45] to exclude individuals with mental health disorders. To estimate menstrual phases for visit schedule, participants will be asked to report their last three menstruation dates to determine average cycle length. Progesterone, estrogen, LH, and FSH levels obtained through bloodwork will be used to confirm cycle phase (follicular phase defined by high estrogen; luteal phase defined by high progesterone). All pre-screening and screening assessments will be performed by trained study stuff and reviewed by the study PI for eligibility. Participants will only be enrolled in the study once eligibility has been determined following the screening visit.

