A recent report has indicated that brain insulin sensitivity differs between sexes, and this may relate to menstrual phases [33]. Specifically, brain insulin sensitivity in females is higher and comparable to lean males during the follicular phase (i.e., right before ovulation when estrogen levels are high) than during the luteal phase (i.e., after ovulation when both estrogen and progesterone levels are high) [33]. and this may contribute to the well-established decrease in whole-body insulin sensitivity in the luteal phase [34,35].

There has yet to be a study that investigates AP-induced insulin resistance in females and the impact of menstrual cycle factors on this relationship. Preclinical evidence of AP-induced disruption in brain insulin action was in male rats only, and previous work aimed at translating these findings did not investigate the effect of menstrual phase [24] It is therefore critical to study the effect of APs on brain insulin action in females, and to examine how it fluctuates with the menstrual cycle.

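### The follicular half of the hormone check relies on high estrogen, which the article also ascribes to the luteal phase, and it may fail early follicular visits that the visit window allows

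*Protocol article*

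**What the plan says.** Under Study design, the article states that "Menstrual cycle phases will be identified using calendar-based counting". Serum progesterone, estrogen, LH and FSH are then measured at every visit to confirm the phase. The Screening visit section gives the only stated criterion for that confirmation: "follicular phase defined by high estrogen; luteal phase defined by high progesterone".

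The Introduction describes the hormonal states that motivate the trial. It places the follicular state of interest "right before ovulation when estrogen levels are high", and the luteal state "after ovulation when both estrogen and progesterone levels are high".

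Study design sets the visit windows. On the follicular side, "The follicular phase visit can take place starting 2 days after the start of the current menstrual cycle", with the gloss that "they will be scanned between days 3 and 11 of their cycle". The luteal window runs from 10 to 3 days before the next onset, glossed as days 18 to 25.

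In the Statistical analysis section, menstrual phase is a factor in the term of primary interest of both mixed models: the two-way interaction with intranasal condition, and the three-way interaction that adds oral condition.

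**The concern.** A rule that confirms one of two phases should be met in that phase and not in the other. The follicular criterion uses a hormone that the article itself calls high in both phases. A visit scheduled as follicular that in fact fell after ovulation would still show high estrogen and would pass.

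The criterion may also err in the other direction. If high estrogen belongs to the days just before ovulation, a visit on day 3 can be truly follicular and still not meet it.

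The hypotheses predict an insulin effect, and its inhibition by olanzapine, in the follicular phase only. The hormone measurements are the only biological check on a label otherwise derived from reported cycle dates. Blood is drawn on the day of scanning, and study staff are unblinded. An ambiguous rule therefore leaves the phase of already acquired scans to judgement, unless it is settled before analysis.

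**Working it through.** The article gives no figure for this check. The working is a comparison of its own statements plus day arithmetic on its windows.

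**Step 1. Apply the rule to the states described in the Introduction.** The first row is inferred; the other two follow from the Introduction, which attributes high progesterone to the luteal phase only.

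| State | Estrogen high | Progesterone high | Meets follicular rule | Meets luteal rule |
|---|---|---|---|---|
| Follicular, before the estrogen rise | no (inferred) | no | no | no |
| Follicular, just before ovulation | yes | no | yes | no |
| Luteal | yes | yes | yes | yes |

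Only the middle row is classified uniquely. The luteal row meets both definitions, and the early follicular row meets neither. The luteal column on its own is correct in all three rows, so progesterone discriminates and estrogen does not.

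**Step 2. Reproduce the windows.** Let L be the cycle length in days. The follicular window ends at L − 17, and the luteal window runs from L − 10 to L − 3. For L = 28 this gives 28 − 17 = 11, 28 − 10 = 18 and 28 − 3 = 25, which matches the article's days 11 and 18 to 25. Counting the next onset as day L + 1 moves each limit by one day and does not change the argument.

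**Step 3. Locate the follicular window relative to ovulation.** The article gives no day of ovulation. Assume 14 days before the next onset, so ovulation falls on day L + 1 − 14 = L − 13. Day 3 is then L − 16 days earlier. The eligibility criteria admit cycles of 21 to 35 days.

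| L | Assumed ovulation day | Day 3 is this many days before | Window ends (L − 17) | End is this many days before |
|---|---|---|---|---|
| 21 | 8 | 5 | day 4 | 4 |
| 28 | 15 | 12 | day 11 | 4 |
| 35 | 22 | 19 | day 18 | 4 |

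Day 3 therefore falls 5 to 19 days before assumed ovulation. In a 28-day cycle the whole window lies 12 to 4 days before it. Moving the assumed ovulation by one day moves these distances by one day. The window opens ahead of the state to which the Introduction attaches high estrogen, and in a 21-day cycle only days 3 and 4 are available.

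**Step 4. Apply a progesterone-only split to the same states.** With not high as follicular and high as luteal, the rows of the first table become follicular, follicular and luteal. Each state receives one phase, and the correct one.

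**Step 5. Number of visits concerned.** Two visits per phase and 15 participants give 2 × 15 = 30 planned visits in each phase, 60 in all.

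**The case against.** The strongest reply is that the hormones are a secondary check. Phase is set by calendar, and staff ask for the date of the last period before each visit. The luteal criterion works. The sentence in the Screening visit section lists four hormones, so its parenthesis may be shorthand for the leading marker of each phase. Numerical cut-offs and the handling of unconfirmed visits may stand in the full protocol, which is not shown. The article nowhere says that estrogen is low on day 3.

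Most of this stands, and it limits the point. Missing cut-offs are not counted here, and the day-3 part is labelled as an inference. The overlap remains: a cut-off for estrogen alone would not resolve it, because the Introduction calls that marker high in both phases. No stated criterion uses LH, FSH or low progesterone to separate them.

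A reader might go further in three ways that the article does not support:

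- **That the hormone check as a whole cannot confirm phase.** High progesterone does separate the luteal phase by the article's own description.
- **That confirmation has no effect on the analysis.** The Statistical analysis section names only menstrual phase as a factor and does not say how unconfirmed visits are treated. The per-protocol sensitivity analysis could exclude them, in which case the faulty rule would help to decide who is left out.
- **That the loss of power can be quantified.** The article gives no mislabelling rate. An early follicular visit is not a luteal one, so it cannot be counted as carrying the luteal effect. A luteal-labelled visit without a progesterone rise is one that the written rule would catch.

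**Conclusion.** The point holds for the follicular half of the rule. As written, high estrogen does not distinguish follicular from luteal visits, by the article's own account of the luteal phase. This part needs no assumption beyond the text. That the criterion may also fail correctly timed early visits rests on two further steps: reading the Introduction as placing high estrogen late in the follicular phase, and an assumed ovulation day for the distances shown.

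The rule bears on all 60 planned visits and on the factor that defines both primary interactions. How many visits it would misclassify cannot be known from the article; the hormone results will show it. This is a correctable conflict in a stated rule, not evidence that the calendar labels are wrong. It should be corrected before analysis.

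**What to change.** Reconcile the Introduction, Study design and Screening visit sections as follows.

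1. **Make progesterone the discriminator.** A visit is confirmed as follicular if progesterone is not high and as luteal if it is high, by the site laboratory's cut-off, fixed in writing before analysis.
2. **Report estrogen as a descriptor** of how late in the follicular phase each visit fell, not as a confirmation criterion. This keeps day-3 visits from being rejected and shows how close the follicular visits came to the state described in the Introduction.
3. **Repeat both mixed models on hormone-confirmed visits** as a sensitivity analysis, reported beside the primary result.

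The cost is analysis text only: all four hormones are already drawn at every visit, and recruitment was still open when the article was submitted. There are two downsides. The confirmed set will hold fewer visits, which matters with 15 participants. Hormones are also drawn on day 2, after both oral doses, so restricting the olanzapine model to confirmed visits selects on a post-dose measurement. For that model the result is supportive only. The concern is smaller for the first model, which uses placebo visits only, with hormones drawn before either intranasal product.
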